### Allocation procedure

After the study researcher measured computer and balances skills for the stratification, he/she will email the therapy secretariat about the results who will then fill in the randomization tables according to the respective strata. Thus the therapy secretariat will be in charge of assigning participants to a group. Patients’ instructions sessions and self-regulated training program will then be planned accordingly and scheduled for the following 10 days of the intervention phase (as per protocol).

### Blinding

Whereas participants and physiotherapists involved in the study will inevitably be aware of the allocation, the outcome assessor (i.e., the study researcher) and the data analyst will be kept blinded to the allocation. The researcher will not be involved in the intervention and the data analyst will be an external professional with no clinical involvement in the trial. Blinding the therapists is generally not possible in exercise trials. To minimize outcome measurement bias, all measurements collected pre- and post-intervention cannot be influenced by therapists providing the intervention nor by the study researcher. The ActiGraph® mobility tracker will measure and save all data directly on the computer in a cryptic version, which will later be analyzed by an external researcher blinded towards participants’ group allocation. Measurements of training volume in the logbook as well as the Falls Efficacy Scale questionnaire are patient-collected data distributing measurement error equally in both groups.

### Sample size

The sample size calculation is based on the observations of a previously performed feasibility study [31] assuming that exergames promoting mobility lead to higher motivation and therefore patients tend to train more often and longer. We assume a statistical power of 0.80 and a medium effect size (d = 0.5). With this effect size of interest in the population, a sample size of 64 subjects per group is necessary to prove any statistical significance. Due to the short observation period of 10 days, less than 10 % drop outs are expected which can be corrected with ITT and multiple imputation of missing data. Alpha is set to 0.05.

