### Trial design

The study will consist of a single blind, stratified, randomized controlled trial with two groups, parallel designs comparing self-regulated conventional exercises with exergames. Participants will be randomly allocated to the intervention group or to the control group, with an allocation ratio of 1:1. Study results will be collected daily during the intervention phase by the participants and at pre- and post-intervention by the study researcher. Figure 1 summarizes the study design. No important changes of methods have been done after trial start.

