## Discussion

According to a database search on PubMed (performed on 06^th^ of June 2015) with the following keywords “exergames”, “serious game”, “elderly people”, “older adults”, “geriatric population” and “randomized controlled trial”, no article could be found on studies comparing any conventional self-regulated exercise program with self-regulated exergames among older post-operative patients. Available studies focus on older adults either suffering from brain injury or cognitive impairment or living in the community.

One of the main characteristics of this trial is its focus on non-supervised exercises. Such self-regulated training has the potential to reach the World Health Organization recommendation for exercise volume in elderly persons over 65 as these can be performed at the person’s own discretion, independently of health care providers. A further focus of this study is on the potential effect of modern game-technology for rehabilitation. We will compare self-regulated exergames with conventional self-regulated exercise programs among elderly post-operative patients. Our hypothesis is that exergames enhance motivation to performed unsupervised exercises thereby leading to increased training volume, and thus to improved balance skills in compared to conventional exercises.

To our knowledge previous studies have focused more on qualitative research than on any clinical outcomes of exergames. The use of game-based technology in elderly users introduces new challenges to the conducting of clinical studies. There is the law of attrition that must be specifically taken into consideration in the evaluation of e-Health trials. Attrition rates are values that indicate participants’ drop out and those might be particularly high in self-help computer-based trials [41]. Special attention must be paid to usage metrics and determinants of attrition in this study with elderly persons, inexperienced in the use of game-based technology. Their measurement and analysis, as well as the characteristics of the subpopulation for which the intervention “works” (in other words, for those who stay in the trial and use it) will be of importance.

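### The 64 per group gives 0.80 power only with complete data; ITT and multiple imputation cannot be assumed to make good the dropout the plan expects

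*Protocol article*

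**What the plan says.** The Sample size section of the protocol article gives the planning values: "We assume a statistical power of 0.80 and a medium effect size (d = 0.5"), and "Alpha is set to 0.05". It does not say whether the test is one-sided or two-sided. From these values it concludes that "a sample size of 64 subjects per group is necessary to prove any statistical significance". The Trial design section allocates patients "with an allocation ratio of 1:1", so the total is 128.

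On loss, the Sample size section points to the ten-day observation period, expects a rate under 10%, and continues: "drop outs are expected which can be corrected with ITT and multiple imputation of missing data". The article states no inflation of the sample size and no recruitment target other than 64 per group.

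The Statistical analysis section returns to missing data. It expects outcomes not to be missing at random and the pattern not to be monotone, and gives this as the reason for multiple imputation. It also plans generalized linear models with covariates such as comorbidity.

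**The concern.** A sample size computed for complete data carries no reserve. Any patient without usable outcome data takes the trial below its stated power unless something else replaces the information. The article names ITT and multiple imputation as that replacement, and neither has this property in general. ITT is a rule about which patients are analysed and in which group. Multiple imputation carries the uncertainty about missing values into the standard error. Without informative partial data or auxiliary variables, its precision is close to that of the observed cases.

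At stake is a figure by which readers will judge the result. If the trial finds no difference, it will be read as having had 0.80 power for d = 0.5, although the plan's own dropout assumption points to somewhat less. The sentence also misdescribes what the two methods do.

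**Working it through.** **Inputs**
- Standardised effect d = 0.5, power 0.80, alpha 0.05, 64 per group, dropout below 10% (10% taken as the ceiling): Sample size section.
- Allocation 1:1: Trial design section.
- Two-sided test: not stated, inferred in step 1.
- Assumption for step 3: a dropout contributes no outcome information, and loss is equal in the two groups.

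**1. Reproduce the plan's figure.** The normal approximation is n per group = 2(z₀.₉₇₅ + z₀.₈₀)² / d² = 2(1.960 + 0.842)² / 0.25 = 62.8, so 63. The two-sample t-test calculation (noncentral t) gives 63.77, so 64. This matches the article. A one-sided test would need 50 by the normal approximation or 51 by the t-test, so only the two-sided t-test reproduces 64.

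**2. Is there any slack?** With 64 complete patients per group the t-test power is 0.801. With 63 it is 0.795. So 64 is the smallest number that reaches 0.80.

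**3. Power after loss.** By the normal approximation, power = Φ(d√(n/2) − 1.960). The t-test values come from the noncentral t distribution.

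| Loss | Complete per group | Normal approximation | t-test |
|---|---|---|---|
| 0% | 64 | Φ(2.828 − 1.960) = 0.807 | 0.801 |
| 5% | 64 × 0.95 = 60.8 | Φ(2.757 − 1.960) = 0.787 | 0.781 |
| 10% | 64 × 0.90 = 57.6 | Φ(2.683 − 1.960) = 0.765 | 0.758 |

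**4. Detectable effect.** With 57.6 complete per group, the t-test calculation gives d = 0.527 for power 0.80, against the planned 0.50.

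**5. Size that would keep 64 evaluable.** At 10% loss: 64 / 0.90 = 71.1, so 72 per group (144 in total). At 5% loss: 64 / 0.95 = 67.4, so 68 per group (136 in total).

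**6. What would have to be true to recover 0.80.** If covariates explain a share R² of the outcome variance, the effective effect is d / √(1 − R²). With 57.6 per group and R² = 0.05, it is 0.5 / √0.95 = 0.513 and power is 0.779. With R² = 0.10, it is 0.5 / √0.90 = 0.527 and power is 0.801. These R² values are assumptions, since the article gives none.

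**7. The missing-data mechanism.** Standard multiple imputation assumes that data are missing at random given the variables in the imputation model. The Statistical analysis section expects the opposite and still infers that multiple imputation is the remedy. On the plan's own expectation, standard imputation therefore cannot be relied on to remove bias, apart from the question of power.

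**The case against.** The strongest reply is that the loss is small and partly recoverable. The expected rate is below 10%, so 0.758 is the worst case on the plan's own assumption, and 5% costs only two points. The primary outcome is recorded daily in a logbook, so a patient who leaves midway may already have supplied several days. The non-monotone pattern the article expects fits intermittent gaps as well as complete loss. Covariate adjustment is planned, and an R² of about 0.10 would bring power at 10% loss back to 0.80.

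Much of this stands. It limits the size of the point and rules out saying that imputation can never recover information. It does not rescue the sentence, because the article neither makes nor quantifies these arguments. It presents ITT and imputation as a correction in themselves.

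Three stronger readings are tempting, and the article does not support them:
- **Much higher attrition.** A reader might set the Discussion's remark about attrition rates, "those might be particularly high in self-help computer-based trials", against the Sample size section and infer a contradiction. The remark is a caution about e-Health trials in general. The lower figure has a reason specific to this trial, a ten-day observation period, and the participants are in-patients with scheduled daily slots. There is tension but no contradiction, and the article gives no basis for loss rates above 10%.
- **Heavy dilution.** A reader might suppose that dropouts are kept in the analysis as having trained zero minutes, which would shrink the effect and cut power further. The plan specifies imputation, not zero-filling. The article also gives no mean or standard deviation of training minutes from which such a loss could be computed.
- **A wrong sample size.** The calculation behind 64 is correct. The fault lies in how loss is treated.

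**Conclusion.** The point holds, and its size is modest. The stated power of 0.80 applies to 64 complete patients per group. On the article's own dropout expectation, power lies between 0.80 and about 0.76: 0.781 at 5% loss and 0.758 at the 10% ceiling, where the detectable effect is d of about 0.53. These figures rest on a two-sided t-test (inferred because it alone reproduces 64), equal loss in both groups, dropouts that contribute no outcome information, and no gain from covariates. Partial logbook data or useful covariates would narrow the gap, but nothing in the article shows by how much.

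The claim that ITT and multiple imputation correct for dropout is not justified as written, and the expectation of data not missing at random weakens it further. The point concerns a stated figure and its justification. It does not show that the design is inadequate.

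**What to change.** In the Sample size section:
- State that 64 per group gives power 0.80 with complete data, and about 0.76 if 10% contribute no outcome data (detectable d about 0.53 at 0.80 power).
- State that the test is two-sided, if that is what was intended.
- Replace the claim that ITT and multiple imputation correct for dropout with a statement that they do not by themselves restore power. If the trial team expects partial logbook days or covariates to recover precision, say so and give the assumed amount.
- Give 72 per group (144 in total) for reference only, as the number that would keep 64 evaluable at 10% loss.

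The cost is a change of wording and a slightly less favourable stated power. Making the statement correct needs no extra patients.

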### Statistical analysis

Data will be analyzed on an intention-to-treat basis using SPSS version 17.1. Missing outcome data is not expected to be at random and the pattern of missing data not to be monotone. Therefore multiple imputation of missing data will be used. This method improves accuracy of subsequent analyses.

Descriptive analysis will be performed of baseline characteristics (such as sex, age, main diagnostic, MMSE) recorded routinely by the medical team in the patient’s file. The changes of the primary and secondary outcome from study inclusion to discharge will be compared in the two groups with generalized linear models accounting for covariates such as comorbidity.

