### Hypotheses

Elderly persons in rehabilitation settings will show higher adherence to self-regulated training when using exergames than when performing conventional exercises.Exergames will lead to greater improvement in balance skills than conventional exercises.

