**Fig. 2 Fig2:**
[figure not shown]
Study time flow. The researcher performs the subjective and objective balance tests (BBS, ActiGraph and FES-I) at the time point T1 (see Fig. 2) and grades the patient’s computer skills. Participants are then stratified into four groups and allocated randomly in the intervention group or the control group. During the two days preceding the start of the self-regulated training program (i.e., time points I1 and I2 in Fig. 2), the patient is instructed on how to perform the self-regulated exercise program according to his allocated group. The intervention period for the self-regulated training program lasts two weeks, namely 10 working days (from Monday to Friday each). On day 11 at the end of the intervention phase (time point T2), the subjective and objective balance skills are again tested by the researcher

In order to ensure safety during self-regulated training, different levels of exercise difficulties in terms of balance and training duration for the conventional program as well as for the exergames were developed. Appropriate exercises will be selected by the physiotherapist according to the patient’s balance skills. The Berg Balance Scale (BBS) test will be used as a cut-off point. A BBS score < 45 indicates a risk of falling, and thus those patients will perform self-exercises in a sitting position only. Patients scoring between 45 and 55 points will perform the exercises in a static standing position, whereas patients reaching the maximum score of 56 will perform exercises in a dynamic standing position. The training program of both groups can be performed either sitting or standing (with or without support), making it accessible to all participants regardless of their balance abilities.

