### Outcome measures

#### Primary outcome

The primary outcome of this randomized controlled trial is the daily training volume of the self-regulated training performed individually. The daily training volume is operationalized by the frequency (quantity of sessions per day) and the total duration (time in minutes of all the performed sessions per day).

It was considered using the log data from the Kinect-based game and Fitbit® to measure daily training volume as well as steps performed. However, as these measurements were not possible in the control group it was decided to use a pro forma logbook in all participants. Patients recorded the number of sessions per day, how many minutes each session lasted and for how many minutes patients went walking.

Patients will also be asked to grade their motivation and enjoyment for each training day, according to a five-level Likert scale, rating respectively from *no motivation/fun* to *huge motivation/fun.* The feasibility of this logbook was tested in a pilot study comparing conventional balance training to Nintendo Wii balance games with stroke patients [31]. A preview of the pro forma logbook is presented in an additional file (see Additional file 2).

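### The planned analysis compares an inclusion-to-discharge change in training volume, but training volume has no value at inclusion and hypothesis 1 concerns its level

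*Protocol article*

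**What the plan says.** The Statistical analysis section gives one between-group comparison, and it covers the primary outcome by name: "The changes of the primary and secondary outcome from study inclusion to discharge will be compared in the two groups with generalized linear models", with adjustment for covariates.

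The Primary outcome section defines that outcome: "The primary outcome of this randomized controlled trial is the daily training volume of the self-regulated training performed individually". It has two components: "The daily training volume is operationalized by the frequency (quantity of sessions per day) and the total duration" in minutes of all sessions that day. Both come from the patient's logbook.

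The timing is given in two places:

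- Trial design: "Study results will be collected daily during the intervention phase by the participants and at pre- and post-intervention by the study researcher".
- Legend to Fig. 2: "The researcher performs the subjective and objective balance tests (BBS, ActiGraph and FES-I) at the time point T1", together with a grading of computer skills. Allocation follows. On the two days before training starts, "the patient is instructed on how to perform the self-regulated exercise program according to his allocated group". Then "The intervention period for the self-regulated training program lasts two weeks, namely 10 working days". On day 11 (T2) the balance measures are repeated.

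The Abstract and the Secondary outcomes section describe assessment before and after the intervention for the secondary outcomes only.

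The first hypothesis reads: "Elderly persons in rehabilitation settings will show higher adherence to self-regulated training when using exergames than when performing conventional exercises".

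**The concern.** A change from inclusion needs a value at inclusion. LDS and FES-I have one. Daily training volume does not: the article describes no record of it before the first intervention day, and the allocated programme is taught only after randomisation. For the primary outcome, the stated analysis therefore asks for a quantity that the described data collection does not supply.

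Someone who follows the sentence must put something in its place. If that is a change within the logbook, the test moves from how much patients train to whether their training rises or falls over two weeks. A patient who trains 50 minutes every day and one who trains 5 minutes every day both score zero. Hypothesis 1 and the rationale in the Sample size section (patients training more often and for longer) both concern the amount of training. A real and steady adherence benefit could then be missed by the only analysis that the article states for it.

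**Working it through.** **1. Reproduce the planned sample size.** Inputs from the Sample size section: d = 0.5, alpha 0.05, power 0.80, 64 per group. Trial design gives 1:1 allocation. Sidedness is not stated.

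- Normal approximation, two-sided: n = 2(1.960 + 0.842)² / 0.5² = 2 × 7.85 / 0.25 = 62.8, so 63 per group.
- Two-sample t-test, two-sided: 63.8, so 64 per group. Power at 64 is 0.801.
- One-sided, the normal approximation gives 50, which does not match.

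The figure of 64 is that of a two-sided comparison of one value per patient. It suits a comparison of levels and is not in question.

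**2. When each outcome is measured**

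| Outcome | Inclusion (T1) | Days 1 to 10 | Day 11 (T2) |
|---|---|---|---|
| Sessions per day, minutes per day | none described | logbook, daily | none described |
| LDS (ActiGraph) | yes | no | yes |
| FES-I | yes | no | yes |

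The inclusion-to-discharge difference exists for the last two rows and not for the first.

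**3. What a change within the logbook estimates.** Let exergames add a constant amount τ to every day's volume. The expected differences between arms are:

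- Mean over 10 days: 10τ / 10 = τ.
- Day 10 minus day 1: τ − τ = 0.
- Week 2 mean minus week 1 mean: τ − τ = 0.
- Least-squares slope: τ × Σ(t − t̄) / Σ(t − t̄)² = 0, because Σ(t − t̄) = 0.

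Every change contrast has expectation zero, so its power equals alpha: 0.05 in total, of which 0.025 favours exergames. This follows by construction from a constant benefit and does not depend on the within-patient correlation.

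**4. Simulation, as a check only.** There were 64 patients per arm, 10 days, and 4000 runs per setting, with the effect scaled so that the 10-day mean differs by d = 0.5. The article gives no daily SD or within-patient correlation ρ. The simulation therefore assumes equal correlation between all days, over a range of ρ. The change shown is day 10 minus day 1.

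| Benefit over the 10 days | ρ | Mean: power | Change: favours exergames | Change: favours control |
|---|---|---|---|---|
| Constant | 0.3 | 0.799 | 0.023 | 0.024 |
| Constant | 0.5 | 0.801 | 0.024 | 0.027 |
| Constant | 0.7 | 0.800 | 0.030 | 0.027 |
| Fades linearly to zero | 0.3 | 0.809 | 0.000 | 0.826 |
| Fades linearly to zero | 0.5 | 0.801 | 0.000 | 0.984 |
| Fades linearly to zero | 0.7 | 0.801 | 0.000 | 1.000 |
| Grows linearly from zero | 0.3 | 0.810 | 0.832 | 0.000 |
| Grows linearly from zero | 0.5 | 0.789 | 0.988 | 0.000 |
| Grows linearly from zero | 0.7 | 0.785 | 1.000 | 0.000 |

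The mean keeps power near 0.80 whatever the time pattern. The change responds to the time pattern alone: the same average benefit gives no signal, a signal against exergames, or a signal for them. The fading and growing rows depend on the assumed ρ and pattern and are illustrations.

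**The case against.** The strongest reply is that the article's intent is clear. The hypothesis, the sample-size rationale and the definition of the outcome all point to a level, and pre/post assessment is reserved for the secondary outcomes. On this view, one sentence in a condensed article has loosely merged two analyses. That is probably how it arose. But the sentence names the primary outcome, and no other sentence gives it a different analysis, so the wording still conflicts with the data described.

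A second reply is that volume in the study programme is zero for everyone before it is taught, so change equals level. This would work arithmetically, and it is why the analysis is not impossible under every reading. The article does not state it.

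A reader might also infer three stronger things that the documents do not support:

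- *That day 10 minus day 1 is the only change the logbook allows.* It is not. A slope or week 2 minus week 1 could equally be computed. The article names none of them, so the low power belongs to a reading of the sentence and not to a contrast that the plan specifies.
- *That ten daily rows per patient will be analysed as independent, inflating the type I error.* The article says only that generalized linear models will be used. It does not fix the data layout or the handling of correlation, and an article commonly leaves these to the fuller plan.
- *That the trial will in fact test the wrong quantity, or is the wrong size.* The first is not shown. The second is contradicted by step 1 of the working.

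**Conclusion.** The point holds as a conflict between stated texts. The only between-group analysis given for the primary outcome is an inclusion-to-discharge change, and the described data collection provides no inclusion value for it. Unless a zero baseline is assumed, the stated change cannot be computed.

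The size of the consequence depends on what replaces it. With a comparison of levels, the design keeps its stated power of 0.80 at d = 0.5 with 64 per arm. With any change within the logbook and a constant daily benefit, power is 0.05. The second figure rests on two conditions, that reading of the sentence and a constant benefit, but on no assumed correlation. Because this concerns the test of the primary hypothesis, it should be settled in writing before the data are analysed.

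**What to change.** Split the sentence in two:

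- **Primary outcome.** Compare training volume between groups as a level over the 10 scheduled training days, in both stated components: sessions per day and total minutes per day. Either one mean per patient or a model of the daily values with patient as the cluster would serve. Session frequency should not be dropped, because the article makes it part of the outcome.
- **Secondary outcomes.** Restrict the inclusion-to-discharge change analysis to LDS and FES-I.

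If a zero baseline was what the authors meant, comparing levels gives the same result and removes the ambiguity. The cost is a sentence or two of wording. It needs no new data, no extra visit and no change to the 64 per group.
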